### Baseline characteristics

Patient characteristics, including gender, height, weight, age, and affected limb, will be collected for subsequent baseline analysis.

### Primary outcome

The primary outcomes measured in this study are Timed Up and Go Test (TUGT) and Hospital for special surgery knee score (HSS).

#### Timed up and go test

TUGT test primarily assesses the individual’s mobility, balance, neuromuscular function, and flexibility. It is common for individuals to experience a reduction in lower limb strength, gait, balance, mobility, and body coordination After TKA, these factors can influence the outcomes of the TUGT test (16). For the experiment, a chair with armrests is prepared and a stopwatch is used. A colored tape is placed 3 meters in front of the chair to serve as a mark line. The participant is instructed to sit upright on the chair, with their back against the backrest and hands on the armrests. Upon hearing the command ‘start’, the participant stands up from the chair and walk towards it as quickly and safely as possible. They walk forward for 3 meters until reaching the marked line, then turn around and return to the chair to sit down. The total time takes for this task will be recorded in seconds. Notes: (1) Participant should wear comfortable clothing and flat shoes during the test. (2) The watch should be started when the participant ‘s back leaves the back of the chair, and stopped when the participant sits down in an upright posture with their back touching the back of the chair. (3) Sufficient time should be given to the subjects to adapt and practice before starting the test, ensuring their understanding of the entire test content. (4) The rater should refrain from offering any verbal encouragement or physical assistance to the participant, but should remain nearby to ensure their safety.

#### Hospital for special surgery knee score (HSS)

In 1976, the Hospital for Special Surgery in the United States proposed this 100-point scoring system. It has been found to have high accuracy in assessing the recovery of joint function after TKA surgery and comparing the pre-and post-surgery outcomes. It is particularly effective in evaluating the motion of both the patellofemoral and femoro-tibial joints, especially in the immediate post-surgery period. HSS is used to assess knee joint function after surgery, mainly including pain, joint range of motion, function, muscle strength, knee joint flexion deformity, and knee joint instability (17). Recovery of the knee joint of the participant is judged by the score, the higher the score, the better.

### Secondary outcome

The secondary outcomes measured in this study are Peak torque of hamstring muscle strength, Knee joint position perception, 3D (Three-dimensional) gait analysis and VAS.

#### Peak torque of hamstring muscle strength

The BIODEX isokinetic muscle strength training system is used to test the maximum torque of the muscle strength (18) third times: before intervention, after intervention and after 4 weeks’ follow-up.

Test method:(1) Participant sits on the isokinetic dynamometer chair. To prevent unnecessary movements, the shoulders, chest, and hips were securely strapped. The cuff of the dynamometer arm was attached near the ankle on the same side. (2) The back seat of the dynamometer was tilted at an angle of 75–85° backward. (3) The angle on the dynamometer was set from 0° (indicating full knee extension) to 90° knee flexion, with a speed of 90°/s. Prior to taking the baseline measurements, each participant performed the movement three times with submaximal effort for practice.

Subsequently, participant is instructed to perform the knee bend movement with maximum effort. Three measurements are taken, and the highest reading obtained is used for data analysis.

#### Knee joint position perception

Using the evaluation software in the isokinetic muscle strength test training system, the participants are evaluated third times: before intervention, after intervention and after 4 weeks’ follow-up.

The test method involved the following steps: (1) Participant sits on the seat with their hips and knees bent at 90 degrees. The participant’s shoulders, waist, and thighs are fixed using shoulder, waist, and thigh fixing belts. (2) The test and evaluation system is calibrated, and the knee joint proprioception test is selected. Two target angles are chosen for the knee joint to flex 30 degrees. The angular velocity of the power head of the constant velocity instrument is set at 1°/s. Each test evaluation is repeated 3 times with a 10 s interval between tests. (3) To avoid visual interference during the test, the participant wears goggles. The participant also holds the electric button. The evaluator instructs the participant to passively raise their calf to the target angle and hold it for 10 s. The participant should remember the current position carefully. After resetting, the instrument will lift the participant’s lower limbs while rotating. When the participant feels that the knee joint angle has reached the target position, they should press the switch. At this point, the instrument stops rotating and records the error between the actual angle and the target angle (19).

Each target angle should be tested 3 times and then the average value is calculated. A smaller recorded error indicates good proprioception. Participants are allowed to familiarize themselves with the procedure once before each test.

#### The 3D gait analysis

The 3D gait analysis is evaluated in the 3D Gait Laboratory of the Rehabilitation Medicine Department of the Second Rehabilitation Hospital of Shanghai. The test will be administered by experienced therapists who are proficient in the steps. During the laboratory session of gait analysis, the patients are instructed to wear tight clothing and walk comfortably.

Test method:(1) Before conducting the experiment, it is important to close all doors and windows and tightly close the curtains to prevent any outside light from entering. In preparation for the experiment, the participants are instructed to remove their shoes and socks and wear tights. (2) The tester then place a reflective marker ball, measuring 14 mm in diameter, on the participant. A total of 48 marker points were selected based on the human body model for both dynamic and static data collections. These marker balls are attached to specific locations on the participant’s body, such as the anterior superior iliac spine, posterior superior iliac spine, lower lateral third of the thigh, lateral condyle of the knee joint, lower third of the lateral manubrium, top of the lateral malleolus, second metatarsal head, and heel. (3) The participants are instructed to walk on a 10-meter-long flat ground at a natural speed. This is repeated three times in total. Kinematic analysis will be conducted for the entire gait cycle, starting from the third trial. Three-dimensional gait quantitative parameters, including spatiotemporal parameters such as pace, stride length, stride frequency, support phase, and knee joint angle, will be recorded and analyzed (20). The data will be analyzed using appropriate software. The participants will be evaluated third times: before intervention, after intervention and after 4 weeks follow-up.

#### VAS (visual analogue scale)

VAS is a widely used pain scoring standard (21). It consists of a 10-point scale, with 0 indicating no pain and 10 indicating severe pain. The intermediate points on the scale represent varying degrees of pain. Patients are asked to mark a point on a horizontal line to indicate their level of pain. Mild pain is represented by 1–3 points, moderate pain by 4–6 points, and severe pain by 7–10 points. Assessing the pain level before and after hamstring training can provide insights into the impact of pain on patients’ gait.

#### Minimizing missing data

In order to avoid and minimize missing data, all participants will receive face-to-face education sessions conducted by qualified doctors upon enrollment. These sessions will cover various topics including potential outcomes after TKA, pain management, and the significance of physical therapy on recovery. Additionally, participants will be informed about potential complications that may arise during the intervention. Regular phone contact will serve as a reminder for participants to stay connected with the study and its evaluation. At 4 weeks’ follow-up, researchers will contact participants via phone and request their presence at the hospital for relevant assessments.

#### Data management

The data will be collected in the Rehabilitation Department of the Second Rehabilitation Hospital of Shanghai and stored in password-protected computer files. Access to these files will be restricted to researchers only. The principal investigator will also maintain a backup copy of all the information. The research findings will be disseminated through related papers. Please refer to Figure 2 for an overview of collection of the different outcomes.

**Figure 2 fig2:**
[figure not shown]
Schedule of enrolment, intervention and assessment.

#### Data monitoring

A supervisor professor among the researchers will closely monitor the participants’ performance throughout the study, including assessment and intervention phases. The supervisor will be unbiased and blind to the group assignments. They will also oversee database management and conduct statistical analysis, while keeping an eye out for any potential adverse events.

Any adverse events that occur during assessment, intervention, or follow-up will be carefully recorded and reported. These adverse events may include symptoms such as increased pain or local redness. The monitoring professor will also ensure the integrity of the data, and The Second Rehabilitation Hospital of Shanghai Data Monitoring Committee will have access to patient assignments.

#### Harm

The study will meticulously document any relevant changes in participant data. In the event of adverse reactions or complications during treatment, these will be reported alongside other trial results.

#### Statistical analysis

SPSS24.0 statistical software was used for the statistical analysis of the data in this study. Data were presented as mean (SD) or median [Q1–Q3] for quantitative variables and frequency (%) for categorical variables. The design includes two groups and three time points. The Shapiro–Wilk test is used to check the normality of the measurement data; if the data do not follow a normal distribution, transformations will be applied. A two-way ANOVA is conducted to determine whether there is an interaction between group and time factors. If an interaction is detected, we will assess whether time or group has an independent effect. If no interaction is detected, we will determine if there are any main effects. Post-hoc comparisons between groups at the same time points are adjusted using Bonferroni correction to ensure the overall type I error rate for each ANOVA does not exceed 0.05. Minimal clinically significant differences (MCID) were applied to compare the present results. The analyzes were conducted intention-to-treat by an independent statistician blinded to group allocation. The significance level is set at α = 0.05.

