### Sample size

Based on the work being done by the team when formulating the plan, we estimated that the difference in TUGT time between the two groups was 1.87 s. With a 2-sided α error of 0.05 and a β error of 0.20, the sample size is estimated at 22 patients in each group. Due to a dropout rate of about 10%, 50 patients are needed.

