### Study outcomes

The patients will be evaluated before rehabilitation training, after four weeks of training and four weeks after intervention (follow-up). Each evaluation will be performed by the same trained doctor for a comprehensive clinical examination and evaluation of outcome indicators. The evaluators will be blinded in this study and will be uninformed about the randomization of the participants or has the opportunity to participate in the research intervention. Adverse events will be recorded throughout the study.

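### The planned two-way ANOVA on group and time names no within-patient term although each patient is measured three times; run as written, its group test is too liberal and its interaction test too conservative.

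*Protocol article*

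**What the plan says.** The Statistical analysis section describes the layout as "The design includes two groups and three time points" and then names the model: "A two-way ANOVA is conducted to determine whether there is an interaction between group and time factors". Main effects are examined if no interaction is found. Comparisons of the groups at each visit are Bonferroni-adjusted "to ensure the overall type I error rate for each ANOVA does not exceed 0.05". The section closes its error specification with "The significance level is set at α = 0.05" and promises an intention-to-treat analysis.

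The three time points belong to the same people. Under Study outcomes: "The patients will be evaluated before rehabilitation training, after four weeks of training and four weeks after intervention (follow-up"). Trial design gives the same schedule.

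The article nowhere mentions repeated measures, a within-subject factor, a patient effect or a mixed model. It names no other model for the two primary outcomes, TUGT and HSS.

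**The concern.** A two-way ANOVA with group and time as its only factors treats each row as a separate, independent observation. Here 44 to 50 patients supply 132 to 150 rows (44 × 3 and 50 × 3), and the three rows of one patient are correlated. A single pooled error then serves for group and for interaction, although the two effects need different ones.

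The plan's decision sequence compounds the problem. The interaction is tested first, with a test that rejects too rarely. A real effect may therefore be passed on to the main-effects step, where the group test rejects too often. Adjusting the post-hoc comparisons cannot repair an F test that has the wrong error term.

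**Working it through.** **Inputs from the article.** Two groups, three visits, alpha 0.05 (Statistical analysis). From the Sample size section: a TUGT effect of 1.87 s, two-sided testing at 0.05 and power 80%, leading to 22 per arm; allowing for roughly 10% dropout, 50 in total.

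**Inputs not in the article.** The within-patient correlation rho: assumed 0.1 to 0.7, equal between all pairs of visits, with equal SD at each visit. The SD of TUGT: back-solved below and needed only for power.

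**1. The plan's own figure.** No SD is stated, so 22 per group can only be inverted. By the normal approximation, SD = 1.87 × √(22/2) / (1.96 + 0.84) ≈ 2.21 s; by the t-test it is about 2.16 s. The dropout step reproduces: 22/0.9 = 24.4, so 25 per group and 50 in total.

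**2. The error each test needs.** Let σ² be the variance at one visit.
- Group: a patient's mean over three visits has variance σ²(1 + 2rho)/3. The pooled error implies σ²/3. The group F is too large by a factor of about 1 + 2rho.
- Interaction: differences between visits within a patient vary in proportion to σ²(1 - rho). The pooled error uses σ². The interaction F is too small, by a factor of about 1 - rho.

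**3. True type I error at nominal 5%.** Large-sample formulas:
- group: 2 × [1 - Φ(1.96/√(1 + 2rho))]
- interaction: P(χ² with 2 df > 5.99/(1 - rho))

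Example at rho = 0.5: 1.96/√2 = 1.386 gives 16.6%; 5.99/0.5 = 11.98 gives exp(-5.99) = 0.25%.

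| rho | group, formula | group, simulated | interaction, formula | interaction, simulated |
|---|---|---|---|---|
| 0.1 | 7.4% | 7.3% | 3.6% | 3.6% |
| 0.3 | 12.1% | 11.9% | 1.4% | 1.5% |
| 0.5 | 16.6% | 16.4% | 0.25% | 0.3% |
| 0.7 | 20.6% | 20.3% | 0.005% | 0.01% |

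The simulations used 20,000 trials per setting with 25 per group; 22 per group gives nearly the same. With first-order autoregressive correlation, or with SDs that change over time, at rho 0.5 to 0.7, the group test runs at 15 to 19% and the interaction test at 0.1 to 1.0%.

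**4. The same data with patient as the error stratum.** Under compound symmetry both tests hold about 5% at every rho tried. Without a sphericity correction, the interaction test rises slightly, to 5.3 to 5.9%, under the autoregressive and unequal-SD settings.

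**5. Power of the interaction test.** This assumes 22 per group, no baseline difference, and 1.87 s at both later visits. The ranges span SD 2.21 to 2.16 s.

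| rho | plain two-way ANOVA | within-patient error term |
|---|---|---|
| 0.3 | 48-51% | 67-69% |
| 0.5 | 46-49% | 82-84% |
| 0.7 | 43-46% | 97% |

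**The case against.** The strongest reply is that a two-way ANOVA with time as a factor is common shorthand for its repeated-measures form. The sequence in the article (interaction, then main effects, then adjusted comparisons at each visit) fits that reading, and nothing rules it out. This stands as a statement of what the authors may intend. It does not settle the matter, because an analyst who follows the text literally would fit the wrong model.

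A condensed article may also leave the covariance structure and sphericity handling to a fuller plan. That is accepted, and their absence is not the complaint. The complaint is that the one model named does not match the design.

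Three stronger readings are tempting and are not supported:
- A reader might infer that the analysis will certainly treat the visits as independent. The article says neither that it will nor that it will not.
- A reader might infer that between-patient variance is missing from the group error. It is present but under-weighted (1 instead of 1 + 2rho). Were it absent, the inflation factor would be (1 + 2rho)/(1 - rho), which at rho = 0.5 gives about 33%, not 16 to 17%.
- A reader might infer that every reported comparison is invalid. Comparing the groups at one visit sets different patients against each other, so within-patient correlation does not invalidate it.

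Finally, rho is an assumption, and at 0.1 the distortion is mild.

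**Conclusion.** The named model does not fit the design, and the wording should be corrected before analysis. If it is run literally, at rho 0.3 to 0.7 the group test operates at roughly 2.4 to 4 times its nominal level (12/5 to 20/5). The interaction test operates at about a third of nominal or far less. The group result conflicts with the article's own 0.05 limit per ANOVA.

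The type I figures depend on the assumed rho and compound symmetry, but the direction also held in the other covariance patterns tried. They do not depend on the SD. The loss of interaction power is less secure: it also rests on a back-solved SD of about 2.2 s and an effect sustained at both later visits. If a repeated-measures ANOVA was intended, the point reduces to saying so.

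**What to change.** Replace the two-way ANOVA by a repeated-measures analysis with patient as the subject. A linear mixed model is preferable: SPSS MIXED, REML, Satterthwaite degrees of freedom, unstructured covariance across visits. It keeps patients who miss a visit, whereas classical repeated-measures ANOVA uses complete cases only. It therefore fits the promised intention-to-treat analysis and the expected dropout of about 10%.

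Model week 4 and follow-up as the outcomes and enter the baseline value as a covariate. Baseline must then leave the outcome vector. Report the group difference at each of the two visits. The interaction-first sequence needs rewording to match, because a sustained effect then appears in the group term rather than in the interaction.

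At minimum, state a repeated-measures ANOVA with time as the within-subject factor and a sphericity correction.

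The cost is a change of wording and slightly more analysis work. No extra patients, visits or data are needed.

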### Randomization procedure and concealment of allocation

Patients who meet the inclusion criteria and are willing to participate will be randomized in a 1:1 allocation ratio after the baseline assessment. SPSS25.0 (IBM Corp., Armonk, NY, United States) statistical software was used to generate random serial numbers. These serial numbers were then printed on cards, sealed in paper envelopes, and the same serial number was written on the outside of each envelope. Patients opened the envelopes in the order of their recruitment. The participants will be randomly divided into two groups: the experimental group (hamstring training group) consisting of 25 cases, and the control group (routine rehabilitation group) consisting of 25 cases. The allocation numbers were concealed in opaque sealed envelopes prepared by a central study coordinator. These envelopes will only be accessible to the central study coordinator, who will open them after obtaining informed consent and baseline measures.

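### In the group-by-time ANOVA the pre-randomisation visit is a level of time, so the no-interaction branch reads a diluted group effect; the interaction branch is undefined

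*Protocol article*

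**What the plan says.** All places are in the protocol article.

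- **Timing.** Under Study outcomes, patients are assessed before training, after four weeks of training, and four weeks after the intervention ends. Under Randomization procedure and concealment of allocation, patients "will be randomized in a 1:1 allocation ratio after the baseline assessment". The first assessment therefore precedes allocation.
- **Model.** Statistical analysis plans a two-way ANOVA on two groups and three time points, starting with the group-by-time interaction.
- **If the interaction is significant:** "If an interaction is detected, we will assess whether time or group has an independent effect".
- **If it is not:** "If no interaction is detected, we will determine if there are any main effects".
- **Per-visit comparisons.** The same section plans post-hoc comparisons of the groups at each time point, Bonferroni-corrected within each ANOVA. They are not tied to either branch.
- **Planned effect.** Under Sample size, "we estimated that the difference in TUGT time between the two groups was 1.87 s". The visit and the SD are not given.

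Baseline is not described as a covariate, and no single visit or test is named as the test of the treatment effect.

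**The concern.** Randomisation makes the expected group difference at baseline zero. A group main effect taken over all three visits gives baseline one third of the weight, so it does not estimate the effect after treatment. A reader who takes it as the treatment effect will understate the benefit.

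The rule also lets a preliminary test decide which quantity is reported. On one side is a diluted average. On the other is a term that could mean main effects, which would be diluted and hard to interpret in the presence of an interaction, or simple effects at each visit, which would not be diluted. Baseline Timed Up and Go and HSS values are collected, yet neither branch is described as giving a baseline-adjusted treatment difference at a stated visit.

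**Working it through.** **Inputs from the protocol.** Difference 1.87 s; two-sided α 0.05; β 0.20; 22 per group; dropout about 10%; 50 in total; three visits, one before randomisation.

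**Assumptions.** The SD is not stated and is back-solved below. The correlation ρ between visits is not stated; it is taken as equal for all pairs, at 0.3, 0.5 and 0.7, with equal variances (so sphericity holds).

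**1. The plan's own figure.** With n = 2(z₀.₉₇₅ + z₀.₈₀)²SD²/Δ², setting n = 22 gives SD = 1.87 × √11 / (1.960 + 0.842) = 2.21 s. The t-test version gives SD = 2.16 s, a standardised effect of 1.87/2.16 = 0.865. Because the SD is solved from the 22, this is not an independent check of it. The dropout step does reproduce: 22/0.9 = 24.4, rounded up to 25 per group, 50 in total.

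**2. Dilution.** The group main effect is the mean of the three visit differences.
- Effect at both post-treatment visits: (0 + 1.87 + 1.87)/3 = 1.25 s.
- Effect at 4 weeks only: (0 + 1.87 + 0)/3 = 0.62 s.

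These values depend on neither the SD nor ρ.

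**3. How often the diluted branch is reached.** The interaction F test has 2 and 2(2n − 2) = 84 degrees of freedom, with noncentrality λ = (n/2) × Σ(δᵥ − mean δ)² / [SD²(1 − ρ)]. For differences (0, 1.87, 1.87) the sum of squares is (2/3) × 1.87² = 2.33; it is the same for (0, 1.87, 0). With n = 22 and standardised effect 0.865:

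| ρ | λ | Interaction power | No-interaction branch reached |
|---|---|---|---|
| 0.3 | 7.8 | 69% | 31% |
| 0.5 | 11.0 | 84% | 16% |
| 0.7 | 18.3 | 97% | 3% |

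With SD 2.21 s the powers are 67%, 82% and 97%.

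**4. The main-effect test taken alone.** The variance of a patient's three-visit mean is SD²(1 + 2ρ)/3. With n = 22 and standardised effect 0.865, power at ρ = 0.3, 0.5, 0.7 is:
- effect at both post-treatment visits: 72%, 63%, 55%;
- effect at 4 weeks only: 25%, 21%, 18%.

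These figures describe that one test, not the whole procedure. In 20,000 simulated trials (SD 2.21 s, sustained effect), the main effect among trials with no significant interaction still averaged about 1.25 s. The dilution is therefore present in the branch where the main effect is read.

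**5. The per-visit comparisons.** Each targets 1.87 s undiluted. If Bonferroni covers three visits, each is tested at 0.05/3 = 0.0167, and power with 22 per arm is 62% (SD 2.21 s) to 65% (SD 2.16 s). One third of α then goes to baseline, where any difference is due to chance.

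**6. Baseline as covariate.** Residual variance at a single visit falls to SD²(1 − ρ²). At α 0.05 with 22 per arm and SD 2.16 s, power for one post-treatment visit is about 84%, 90% and 98% at ρ = 0.3, 0.5, 0.7.

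**The case against.** A reader might infer that both branches end in main effects, so that the treatment effect is always diluted. The text does not support this. It uses a different term in each branch, and simple effects are the usual follow-up to an interaction. What can be said is that the term in the interaction branch is undefined.

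A reader might also set the 63% for the main effect against the 90% for a covariate-adjusted comparison (both at ρ = 0.5) and conclude that the plan loses that much power. That does not follow. The plan tests the interaction first, and with baseline as a level of time this is a valid test of differential change. It has about 84% power at ρ = 0.5, and the main effect is read only when it fails.

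The per-visit comparisons answer part of the point, since they give undiluted group differences at 4 weeks and at follow-up. But they are called post-hoc, are not described as baseline-adjusted, are not named as the treatment test, and may spend α on baseline.

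Strictly, the main effect is an unbiased estimate of the three-visit average; it misleads only when read as the post-treatment effect. It is also fair that not using ANCOVA is no error in itself, and that an article may leave covariates to a fuller analysis plan. The decision rule, however, is stated in the article, and the difficulty lies in that rule.

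**Conclusion.** The point holds in a limited form. In the no-interaction branch the group effect is diluted to two thirds of its post-treatment size if the effect is sustained (1.87 s becomes 1.25 s), and to one third if it is present only at 4 weeks (0.62 s). These fractions follow from randomisation after baseline and three equally weighted visits. The interaction branch has no defined meaning as written.

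How often the dilution would matter rests on assumptions: about 31%, 16% or 3% of trials at ρ = 0.3, 0.5 or 0.7, with 22 per arm and a standardised effect of 0.865 implied by the planned sample size. The documents do not show that every route through the plan is diluted, nor that overall power falls to the main-effect figures.

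**What to change.** For Timed Up and Go and for HSS, replace the interaction-then-main-effect rule with one repeated-measures model:

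- outcomes: the 4-week and follow-up values;
- covariate: the baseline value of the same measure;
- terms: group, visit, and group-by-visit.

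Report the adjusted group difference with its 95% confidence interval at each post-treatment visit. Name one visit in advance as primary; the choice is the investigators' and should match the visit to which the 1.87 s refers. Do not test group differences at baseline.

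The cost is a change of analysis wording. All the data needed are already collected, and no visit, procedure or patient is added.

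### TUGT and HSS are both primary, but type I error is controlled only within each outcome's ANOVA, and no success rule, order or decisive visit is given; if either outcome suffices, trial-level error is about 8–10%.

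*Protocol article*

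**What the plan says.** Protocol article, Primary outcome: "The primary outcomes measured in this study are Timed Up and Go Test (TUGT) and Hospital for special surgery knee score (HSS"). The abstract names the same pair. Neither place ranks them.

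Study outcomes sets three assessments: "The patients will be evaluated before rehabilitation training, after four weeks of training and four weeks after intervention (follow-up"). None is singled out as the one on which the trial is judged.

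Statistical analysis: "A two-way ANOVA is conducted to determine whether there is an interaction between group and time factors". Main effects are examined when no interaction is found. Between-arm post-hoc contrasts at a given visit are "adjusted using Bonferroni correction to ensure the overall type I error rate for each ANOVA does not exceed 0.05". The section adds: "The significance level is set at α = 0.05".

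Sample size rests on TUGT alone: "we estimated that the difference in TUGT time between the two groups was 1.87 s", and "With a 2-sided α error of 0.05 and a β error of 0.20, the sample size is estimated at 22 patients in each group". It gives no SD, no visit for that difference and no calculation for HSS.

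**The concern.** The article does not leave multiplicity open. It states a rule and sets its reach at one ANOVA. With two primary outcomes there are two ANOVAs, so the rule stops one level short of the primary conclusion. Nothing states whether the trial succeeds on TUGT or HSS, or only on both.

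Two further choices stay open until the data are seen. One is which visit carries the claim. The other is which test carries it: the interaction, the group main effect or a post-hoc contrast. The Bonferroni step covers only the last of these.

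At stake is the strength of a positive headline. A reader who sees a significant primary outcome will assume a 5% false-positive rate, and under an either-outcome reading the rate is higher.

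**Working it through.** **Inputs.** From the article: two primary outcomes; 2 groups × 3 times; α = 0.05 per ANOVA; 22 evaluable per arm; power 0.80; TUGT difference 1.87 s; dropout about 10%. Assumed, because the article does not give them: the correlation between the two outcomes (0 to 0.7) and, in the simulation, a correlation of 0.6 between visits within an outcome.

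**1. The plan's own figure.** No SD is stated, so 22 per arm cannot be checked forwards. Solving backwards, SD = 1.87 / [(1.960 + 0.842) × √(2/22)] = 1.87 / 0.845 = 2.21 s (2.16 s with the t distribution). For dropout, 22 / 0.9 = 24.4, rounded up to 25 per arm, or 50 in total, which agrees with the article. The error-rate results in steps 2 to 4 do not depend on this SD.

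**2. Two primaries at 0.05, either sufficing.** If independent, 1 − 0.95² = 0.0975; the upper bound is 0.05 + 0.05 = 0.10. For correlated test statistics, 1 − P(|Z₁| < 1.96 and |Z₂| < 1.96), bivariate normal:

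| Assumed correlation | Error over both outcomes |
|---|---|
| 0 | 0.0975 |
| 0.3 | 0.095 |
| 0.5 | 0.091 |
| 0.7 | 0.0835 |

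**3. By the test that carries the claim.** The 2 × 3 repeated-measures ANOVA was simulated under the null with 22 per arm and 20,000 runs per setting. A positive result on either outcome counts:

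| Route to a claim | Outcome correlation 0 | Outcome correlation 0.7 |
|---|---|---|
| Interaction test alone | 0.095 | 0.081 |
| Post-hoc contrasts, Bonferroni over 3 visits | 0.084 | 0.074 |
| Interaction or group main effect | 0.188 | 0.156 |

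For a single outcome, the post-hoc route alone gives 0.042 to 0.044, so the promised 0.05 per ANOVA holds for those contrasts. Interaction or main effect gives about 0.097 to 0.099 for a single outcome.

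The post-hoc row counts the baseline contrast as one of three. If only the two post-baseline contrasts can support a claim and the divisor stays at three, the bound over both outcomes is 4 × 0.05/3 = 0.067. If the divisor is two, four independent contrasts give 1 − 0.975⁴ = 0.096.

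**4. If both must succeed.** The chance that both are falsely significant cannot exceed 0.05, so there is no inflation.

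**5. Cost of splitting alpha.** At 0.025 for TUGT and SD 2.21 s, power with 22 per arm is Φ(1.87 / (2.21 × √(2/22)) − 2.241) = Φ(2.80 − 2.24) = Φ(0.56) = 0.71. Keeping 80% needs 2 × (2.241 + 0.842)² × (2.21/1.87)² ≈ 26.6, so 27 per arm. With dropout this is 27 / 0.9 = 30 per arm, or 60 in total.

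**The case against.** **The article promises control per ANOVA, not per trial.** This stands. The sentence on Bonferroni is not false; its reach is too narrow for two primaries.

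**The inflation depends on an either-or rule that the article does not state.** This also stands, so the 8–10% is conditional. Equally, no both-must-succeed rule is stated, and the sample size shows power for TUGT only, which does not suggest that joint success was planned for.

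**The outcomes are probably correlated.** This is plausible: the Discussion describes TUGT and HSS together as measuring overlapping abilities. It lowers the figure to about 8–9%, not to 5%.

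**Success rules often sit in an analysis plan that is not shown.** This has some force for the missing order and visit. It does not cover the stated rule, which the article itself fixes at the level of one ANOVA.

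**Stronger readings that the documents do not support.** A reader might infer that every visit is tested at an uncorrected 0.05, giving 1 − 0.95⁴ = 0.185 for two outcomes at two visits. The article does the opposite: visit contrasts are Bonferroni-adjusted within each outcome, so the visits do not add to the doubling by that route. The open question about time is only that no visit is named as decisive.

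A reader might also take 16–19% as the plan's actual error rate. That requires either omnibus test alone to justify a claim of benefit, which the article does not say. It also rests on a repeated-measures model with equal correlation between visits, whereas the article says only two-way ANOVA.

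**Conclusion.** The point holds in a limited form. Two unranked primaries are each given a full 0.05, and the plan has no success rule, order, alpha split or decisive visit. If either outcome supports the primary claim, the trial-level error is about 8–10%. It comes close to double the 0.05 level only when the tests are nearly independent. If only the adjusted post-hoc contrasts decide, it is about 7–8% with three contrasts per outcome. Figures of 16–19% are an upper scenario in which the interaction or the group main effect also counts as success. Requiring success on both outcomes would remove the inflation, but the plan does not adopt that rule. The correlations behind these ranges are assumptions.

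**What to change.** Before unblinding, name one decisive test: the between-group TUGT contrast at one pre-specified visit, two-sided 0.05. TUGT is the outcome on which the trial was sized. The end of the 4-week intervention is one candidate visit; the Sample size section names none, so the sponsor must state to which visit the 1.87 s refers.

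Test HSS at the same visit only if TUGT is significant (fixed sequence, each at 0.05). Label the other visit, the interaction test and the main effects as supportive. This holds the error over the two outcomes at 0.05.

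Cost: wording in the Primary outcome and Statistical analysis sections, and HSS loses equal status. TUGT keeps its full 0.05, so the 50 patients stand.

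Alternatives, each with its price:
- **Co-equal, either sufficing:** Holm across the two contrasts at the named visit. Its first step is at 0.025, where TUGT has about 71% power with 22 evaluable per arm at the implied SD, unless HSS is also significant. Keeping 80% at 0.025 takes about 27 evaluable per arm, or 60 patients in total.
- **Both required:** each at 0.05 with no alpha penalty, but power for HSS must then be shown.
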